#### Neuroimaging data analysis

SPM12 software will be used to perform paired *t*-tests on the acquired ReHo value. The statistical threshold voxel-level will be *P* < 0.001 with multiple comparisons corrected by FEW (family-wise error), cluster level α < 0.05. More than 10 continuous voxels will be significant.

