## Methods

### Study setting

This is a prospective functional neuroimaging and neurotic electrophysiological study with a case-control design between the PSD with the HC groups and a randomized controlled design within the 3 PSD groups (OAKT group, ocular acupuncture group, and kinesitherapy group). Using fMRI scanning and the TMS-MEP technique, we will assess the central-peripheral neuronal function changes of PSD as well as the coupling effects of OAKT on them. This trial was authorized by the Institutional Review Board of Chengdu University of Traditional Chinese Medicine in April 2022 (reference number: 2022KL-027) and registered (ChiCTR2200060483) at the Chinese Clinical Trial Registry in June 2022. We plan to enroll 90 participants at the Hospital of Chengdu University of Traditional Chinese Medicine from Aug 31, 2022, to Dec 31, 2023. All eligible subjects will be evaluated by fMRI scanning, TMS-MEP examination, and the MMT and Fugl-Mayer assessment following enrollment and on the last day after 4-weeks of waiting (for HC subjects) or intervention (ocular acupuncture, kinesitherapy, or OAKT for PSD subjects, respectively). MMT and Fugl-Meyer score, ReHo value, cluster size, active or positive brain regions and their MNI coordinates, amplitude (AMP), potential latency (PL), and central motor conduction time (CMCT) in the cortical region will be measured, and Pearson correlation analysis will be performed to assess the relationship between clinical and imaging outcomes. This trial will be conducted in accordance with the Standard Protocol Items: Recommendations for Interventional Trials (SPIRIT) (43). Figure 1 displays a flow diagram.

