Regional homogeneity (ReHo), a typical fMRI analysis, can indirectly reflect the time synchronization of spontaneous neural function activities in a specific brain region. The Kendall's Coefficient Concordance (KCC) will be used to quantify the local consistency of time series between each voxel in the entire brain and the nearest 26 voxels around it by using REST software in Matlab. Each individual receives a ReHo image by computing the KCC value of each voxel. After normalization, the average ReHo image of each subject will be derived by dividing the KCC value of each voxel by the average KCC value of the entire brain. The estimated ReHo value corresponds to the KCC value, which runs from 0 to 1. The closer it is to 1, the more consistent this voxel's activity is in time series with its neighboring voxels, reflecting brain local neuronal activity synchronization. The calculation is expressed as follows:

$$\begin{array}{l} \text{ReHo}=\frac{\sum {\left({\text{R}}_{\text{i}}\right)}^{2}-\text{n}{\left(\text{R}\right)}^{2}}{{\text{k}}^{2}\left({\text{n}}^{3}-\text{n}\right)/12} \end{array}$$

The SPM12 in Matlab will be used to analyze the obtained ReHo value. MNI coordinates of the associated regions, the size of the clusters, and the active or positive brain regions will all be noted before and after the intervention.

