#### Clinical and electrophysiological data analysis

SPSS 23.0 will be used for data analysis. For measurement data, the *T*-test or ANOVA with 95% confidence intervals will be used to compare groups if the distribution is normal, else a Non-parametric Test will be performed. For enumeration data, a chi-square test will be used. A two-sided threshold of *P* < 0.05 will be considered statistically significant.

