Two advances in this study are the idea and the methodology. For the idea, we propose to conduct a prospective functional neuroimaging and neurotic electrophysiological study based on a case-control study in the PSD and HC groups as well as a self-control study in the PSD group. The primary motor cortex (higher center), the thalamus (higher center), the spinal cord (secondary center), and the muscle (peripheral) motor neural signal transmission channel are the targets of our assessment of PSD's abnormal central-peripheral neural function and the coupling effects of OAKT on PSD. For the technique, we propose doing a curative effect evaluation and mechanism investigation based on fMRI scanning, TMS-MEP examination, and the MMT and Fugl-Mayer scale assessment to examine the effects of OAKT on brain function, motor nerve function, and degree of motor dysfunction in PSD. Pearson analysis will also be performed between the MMT score, Fugl-Meyer score, and ReHo values of PSD to investigate the association of imaging, neurotic electrophysiological, and clinical outcomes, and to finally exploit the central-peripheral linkage control mechanism and coupling effect of OAKT on PSD from functional imaging and neurotic electrophysiology perspectives.

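### The stated ReHo test is a paired t-test, read as pre-post; no test of OAKT against OA or KT is specified, and none of PSD against HC clearly so

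*Protocol article*

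**What the plan says.** In the protocol article, Neuroimaging data analysis names one test: "SPM12 software will be used to perform paired *t*-tests on the acquired ReHo value". It adds a threshold: "The statistical threshold voxel-level will be *P* < 0.001 with multiple comparisons corrected by FEW (family-wise error), cluster level α < 0.05". It does not say what is paired with what, but Functional neuroimaging outcomes says that "the active or positive brain regions will all be noted before and after the intervention", which points to pre-post pairing.

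The tests meant for comparing groups stand under another heading, Clinical and electrophysiological data analysis, and are run in SPSS: "the *T*-test or ANOVA with 95% confidence intervals will be used to compare groups if the distribution is normal". The only other analysis of ReHo is a covariate-adjusted Pearson correlation with MMT and Fugl-Meyer scores in patients, which contrasts no groups.

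The Abstract and Study setting describe a case-control comparison of PSD with HC and "a randomized controlled design within the 3 PSD groups (OAKT group, ocular acupuncture group, and kinesitherapy group". Study setting gives the aim for fMRI and TMS-MEP together: "we will assess the central-peripheral neuronal function changes of PSD as well as the coupling effects of OAKT on them". The Discussion describes the design differently: "a case-control study in the PSD and HC groups as well as a self-control study in the PSD group".

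**The concern.** The design poses two imaging questions: whether patients differ from healthy controls, and whether OAKT changes brain function beyond what its components do. The second is inferred from the randomised design, since no objective states it in those words. Both are between-group questions.

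Patients enter with a newly diagnosed stroke and are rescanned after 4 weeks. A change within the OAKT arm therefore combines the treatment effect with spontaneous recovery, regression to the mean and any scan-to-scan drift. Healthy controls are also scanned twice, so they could estimate drift, but they have no stroke to recover from. Only the randomised OA and KT arms carry the same recovery, and the stated ReHo analysis never sets OAKT against them.

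If the results appear as three within-arm maps, it is natural to read a cluster seen under OAKT but not under KT as specific to OAKT. That reading has no test behind it.

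**Working it through.** **1. Which stated analysis serves which question**

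| Question | Clinical and TMS-MEP data | ReHo maps |
|---|---|---|
| OAKT vs OA, OAKT vs KT | t-test, ANOVA or non-parametric test | none stated |
| PSD vs HC | same | none clearly stated |
| Before vs after, within group | not singled out | paired t-test |
| Association with clinical scores | not applicable | Pearson correlation, PSD only |

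**2. The plan's own figure.** Sample size gives 15 + 15 + 15 + 45 = 90, which reproduces. The document states no power, effect size or standard deviation, so everything below rests on assumed values.

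**3. Why separate paired tests do not compare arms.** Let all three arms have the same true change and let each paired test have power p. The arms are different patients, so the tests are independent.

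- OAKT significant and at least one comparator not: p × (1 − p²).
- OAKT alone significant: p × (1 − p)².

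| Assumed p | p(1 − p²) | p(1 − p)² |
|---|---|---|
| 0.3 | 0.3 × 0.91 = 0.273 | 0.3 × 0.49 = 0.147 |
| 0.5 | 0.5 × 0.75 = 0.375 | 0.5 × 0.25 = 0.125 |
| 0.7 | 0.7 × 0.51 = 0.357 | 0.7 × 0.09 = 0.063 |

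**4. The same at n = 15 per arm.** Power of a paired t-test is taken from the noncentral t distribution with 14 degrees of freedom and noncentrality d√15, where d is mean change divided by the SD of change. The test is at one location and two-sided (the plan gives no sidedness for imaging).

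| Level | d | Power p | p(1 − p²) |
|---|---|---|---|
| 0.05 | 0.3 | 0.192 | 0.185 |
| 0.05 | 0.5 | 0.438 | 0.354 |
| 0.05 | 0.8 | 0.821 | 0.267 |
| 0.001 | 0.3 | 0.010 | 0.010 |
| 0.001 | 0.5 | 0.045 | 0.045 |
| 0.001 | 0.8 | 0.223 | 0.212 |
| 0.001 | 1.0 | 0.442 | 0.356 |

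At the plan's voxel level of 0.001 the misleading pattern is rare for small and moderate effects and common only for large ones. The cluster-level correction is not modelled.

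**5. Power of the missing contrast.** Two-sample t-test on change, 15 vs 15, noncentral t with 28 degrees of freedom, where d is now the difference in mean change divided by the SD of change:

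| d | Two-sided 0.05 | Two-sided 0.001, uncorrected |
|---|---|---|
| 0.5 | 26% | 2% |
| 0.8 | 56% | 10% |
| 1.0 | 75% | 21% |
| 1.2 | 89% | 38% |

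**The case against.** The article is condensed, and its imaging paragraph does not say that paired tests are the only ones; second-level models could sit in a plan not shown. This carries limited weight. The article does name the imaging test, and it gives between-group tests for the other outcomes, so the reader is left with a stated test that does not answer the randomised question.

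Four stronger readings are tempting, and the document does not support them.

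- A reader might infer that a paired test can never compare patients with controls. Sample size says that the 45 controls are to be matched, and a paired test across individually matched pairs would be valid. However, no one-to-one pairing or matching variables are stated, and the outcome section points to pre-post pairing. On either reading OAKT against OA or KT remains untested.
- A reader might infer that the healthy controls contribute nothing to the longitudinal question. They are assessed twice and can estimate scan-to-scan drift, though not stroke recovery.
- A reader might infer that randomisation goes unused altogether. The clinical and TMS-MEP outcomes do have between-group tests.
- A reader might take the chance that the three arms disagree, 1 − 0.5³ − 0.5³ = 75% at p = 0.5, as the rate of false evidence for OAKT. Half of it (0.75 − 0.375 = 0.375) has OAKT non-significant and could not suggest an OAKT effect.

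It is also fair to say that no passage announces an intention to compare significance patterns across arms, and that Sample size calls this a mechanism study rather than a clinical trial. Attributing a mechanism to OAKT still needs a contrast with its components.

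**Conclusion.** The point holds as a mismatch between the declared design and the stated imaging test. The only group or time test given for ReHo is a paired t-test, apparently pre-post. No OAKT-OA or OAKT-KT test is specified, and no PSD-HC test is clearly specified. Followed as written, the analysis would not separate an OAKT effect on ReHo from recovery after stroke. This is a limit of the stated analysis, not of the data: the randomised scans would support the comparison once a between-arm test is added.

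The conclusion rests on the text and needs no assumed effect size. The illustrated size does: 27%, 37.5% and 36% for OAKT significant with at least one comparator not, and 15%, 12.5% and 6% for OAKT alone, at assumed power 0.3, 0.5 and 0.7 with identical true change in all arms. At an uncorrected 0.001, the first of these chances is 1% at d = 0.3 and 4.5% at d = 0.5, and reaches 36% only at d = 1.0.

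**What to change.** In Neuroimaging data analysis, specify:

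- for treatment, a three-arm between-group model on ReHo change (the group-by-time effect), with prespecified OAKT-KT and OAKT-OA contrasts;
- for case-control, a two-sample PSD-HC comparison of baseline maps adjusted for age and sex, or a paired comparison if matching is truly one-to-one, in which case the matching should be described;
- the stated family-wise correction for both.

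State that the paired t-tests are pre-post within arm, and keep them as descriptive. Reconcile the Discussion's wording, "as well as a self-control study in the PSD group", with the randomised design in Study setting. Clarifying is enough, because pre-post assessment can coexist with randomised arms.

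The cost is wording only: same patients, scans and software. The downside is power. With 15 per arm the between-arm contrast has about 56% power at an assumed d = 0.8 (one location, two-sided 0.05) and about 10% at 0.001, so imaging conclusions about OAKT become more cautious and should be reported with their uncertainty.

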#### Functional neuroimaging outcomes

A 3.0 Tesla high-field full-body magnetic resonance imaging system will be used for functional neuroimaging. Bold-fMRI data is acquired in the resting state following structural image scanning with a three-dimensional fast-spoiled gradient-recalled sequence and functional image scanning with a Gradient-Echo-Planar Imaging for 10 min, covering the entire brain, cerebellum, and brain stem. The parameters for scanning structural images include layer a thickness of 1 mm, a Repetition Time/Echo Time (TR/TE) of 2,700 ms/3.39 ms, Field of Vision (FOV) of 256 mm^2^, Matrix of 256 × 256, a Flip Angle of 7°, and an in-plane resolution of 1 × 1 mm. The settings for functional image scanning include a slice thickness of 5 mm, a TR/TE of 2,000 ms/30 ms, Matrix of 64 x 64, FOV of 240 mm^2^, and a Flip Angle of 90°.

The original fMRI data in DICOM format will be copied to a computer and converted by MRIcro software into an analyzable.img file format. The software packages Data Processing Assistant for Resting-State fMRI (DPARSF) and the statistical parametric mapping software package (SPM12) in Matlab (Mathworks, Inc., Natick, Massachusetts) will be utilized to preprocess the fMRI data. Preprocessing steps include (1) realign, all images of each selected subject whose translation in all directions (x, y, z) is <1 mm and rotation angle is <1 degree will be aligned with its first image for further analysis; (2) Spatial normalization, registers images of all subjects to the standard template of Montreal Neurological Institute (MNI) neurological spatial coordinates and re-cuts the voxel to 3 mm 3 for data standardization and individual comparability; (3) slice-timing correction, uses a mathematical approach to collect all images at the same time point by default, with the intermediate time point as the reference layer; (4) smoothing with an 8 mm full width at half maximum (FWHM) kernel to reduce spatial noise, as well as errors caused by spatial normalization; (5) Detrending with linear regression and filtering with a frequency window of 0.01–0.08 Hz to remove low frequency noise caused by respiration, heartbeat, and other physiological factors, as well as high frequency noise from the MRI scanner itself.

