### Sample size

This is a central-peripheral coupling mechanism study rather than a clinical trial. As human-based neuroimaging mechanism studies differ from clinical trials, sample size cannot be estimated using clinical trial computational methods. According to the sample size calculation of imaging studies at home and abroad (47), the sample size is usually 6–12 cases in each group. We determined the sample size as 15 cases per group in accordance with the minimum statistical requirements, considering the drop-out that could be brought on by subjects' compliance and removing the scenario that patients' excessive head movement might influence the data in the statistical analysis progress during fMRI scanning. To keep the statistical results accurate and reliable, 45 healthy controls must be matched simultaneously. In total, 90 subjects-−15 in the OAKT group, 15 in the OA group, 15 in the KT group, and 45 in the HC group—are required for this study.

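### The neuroimaging threshold pairs cluster-level family-wise α < 0.05 with a fixed 10-voxel rule that does not match it, and the plan does not say which one decides significance

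*Protocol article*

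**What the plan says.** All of this is in the protocol article. Under Neuroimaging data analysis, the test is given as "SPM12 software will be used to perform paired *t*-tests on the acquired ReHo value". The threshold follows: "The statistical threshold voxel-level will be *P* < 0.001", with "multiple comparisons corrected by FEW (family-wise error), cluster level α < 0.05". The next sentence reads "More than 10 continuous voxels will be significant". The section does not say whether the 10-voxel extent is an added minimum, a rule that suffices alone, or the extent thought to deliver the 0.05. It gives no smoothness estimate, search volume or derivation of the number 10.

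The inputs that govern cluster size are under Functional neuroimaging outcomes. Preprocessing includes "smoothing with an 8 mm full width at half maximum (FWHM) kernel" and resampling ("re-cuts the voxel to 3 mm 3 for data standardization"). ReHo is then computed as the concordance between "each voxel in the entire brain and the nearest 26 voxels around it". The group size comes from Sample size: "We determined the sample size as 15 cases per group".

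**The concern.** As worded, the last sentence is a sufficient condition: any cluster above 10 voxels counts as significant. Cluster-level family-wise correction works differently, because the critical extent rises with the smoothness of the map and the volume searched. The two rules therefore agree only if the critical extent happens to be about 10 voxels. Where it is larger, a cluster between 11 voxels and the critical extent passes one rule and fails the other.

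The list of significant regions is at stake. Functional neuroimaging outcomes says that regions, their MNI coordinates and cluster sizes will be recorded before and after the intervention. An unclear rule leaves the choice open until the maps have been seen. The correlation section does not say that its ReHo values come from significant clusters, so an effect on the correlations is possible but not established.

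**Working it through.** **The plan's own figure.** The 0.05 is nominal, set by the family-wise correction. The article does not derive it from the 10-voxel extent, so there is nothing to reproduce. The check asks what error rate the extent rule would have if it decided significance by itself.

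**Inputs from the article.** Paired t-test with n = 15, so 14 df; cluster-forming P < 0.001, which is t > 3.79 per direction; voxels taken as 3 × 3 × 3 mm = 27 mm³; extent above 10, so at least 11 voxels or 11 × 27 = 297 mm³; 8 mm smoothing listed before ReHo; 27-voxel ReHo neighbourhood.

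**Assumptions not in the article.** Search volume 45,000 to 60,000 voxels; smoothness of the tested map 6.5 to 12 mm FWHM. Sidedness is not stated, so rates are shown for one direction and for both.

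**Scale.** One 8 mm resolution element is 8³ = 512 mm³, or 512/27 ≈ 19 voxels. Ten voxels (270 mm³) are about half of that.

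**Random-field check (60,000 voxels, 8 mm, 14 df, one direction).**
- Expected clusters under the null, from the t-field Euler characteristic densities: E[m] = 50.1.
- Expected suprathreshold voxels: E[N] = 60,000 × 0.001 = 60.
- Cluster-size distribution: P(size ≥ k) = exp(−βk^(2/3)), with β = (Γ(5/2) × E[m]/E[N])^(2/3) = (1.329 × 50.1/60)^(2/3) = 1.110^(2/3) = 1.072.
- At k = 10: exp(−1.072 × 4.642) = 0.0069. The expected number of such clusters is 50.1 × 0.0069 = 0.346.
- P(at least one) = 1 − exp(−0.346) = 0.29. Both directions: 1 − (1 − 0.292)² = 0.50.
- Extent that holds 5%: 50.1 × exp(−βk^(2/3)) = −ln(0.95) = 0.0513, so k^(2/3) = ln(50.1/0.0513)/1.072 = 6.42 and k ≈ 16.

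**Simulation.** Gaussian null volumes, n = 15, 18-connectivity, 400 to 500 runs per setting (Monte Carlo standard error about 2 points). At the same setting it gives 0.30 for one direction, in agreement with the 0.29 above.

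Results if more than 10 voxels at P < 0.001 were the whole rule. Ranges pool the assumed search volumes; the 12 mm row combines simulation and random-field values.

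| Map smoothness | One direction | Both directions | 5% extent, one direction (voxels) |
|---|---|---|---|
| 6.5 mm | 3-6% | 7-11% | 10-11 |
| 7 mm | 7-11% | 15-20% | 11-12 |
| 7.5 mm | 17-19% | 28-34% | 13-14 |
| 8 mm | 24-33% | 42-58% | 16-18 |
| 10 mm | 53-65% | 77-88% | 24-27 |
| 12 mm | 68-80% | 91-96% | 37-40 |

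**Sensitivity to n at 8 mm.** With 12 patients (an assumed number after drop-out) the rates are 21-26% and 36-44%. With the 45 healthy controls and 45,000 voxels they are 40% and 66%.

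**Which rows are plausible.** Noise was passed through the listed order: 8 mm smoothing, 0.01-0.08 Hz filter, then 27-voxel concordance. The ReHo maps had a smoothness of about 6.5 mm, or 6.8 to 7.5 mm when 5 to 7 mm of intrinsic smoothness was assumed. If the smoothing were instead applied after ReHo, which is not the order listed, the maps had about 9.3 mm. The kernel width is therefore not a floor for the smoothness of the tested map.

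**The other reading.** If a cluster must pass family-wise P < 0.05 and also exceed 10 voxels, the second condition can only remove clusters. The rate stays at or below the nominal 5%.

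**The case against.** A reader might infer that the 10-voxel sentence contradicts the family-wise correction outright, and that the analysis will run far above 5%. The article does not support that. The correction is named first, and nothing says that the next sentence replaces it. The sentence can be read as a minimum extent on clusters that already pass, or as an extent filter after a voxel-level corrected P < 0.001. Neither reading inflates the error. Every rate in the table describes an analysis in which the named correction does not decide.

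The size is also conditional. Smoothness and search volume are assumed, and the listed order of steps points to the lower rows. At 6.5 mm the 5% extent is about 10 voxels, the article's own number, and the one-direction excess is small or absent.

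Both parts of the objection stand, and they rule out an unconditional claim of lost error control. They do not rescue the wording. The article states a decision rule rather than leaving it to a fuller document, and read literally that rule makes the fixed extent sufficient. The absence of a stated correction for testing both directions, or for repeating the test in three arms, is a separate matter and not part of this error.

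**Conclusion.** The section states two significance criteria that do not match, without saying which governs. There is no harm if 10 voxels is an added minimum. If it is used as worded, or treated as the extent that yields α < 0.05, the whole-brain false-positive rate exceeds 5% in nearly all settings tried. The excess is slight near 6.5 mm map smoothness, moderate at 7 to 7.5 mm (7-19% per direction) and large from 8 mm upward (24% or more per direction). These figures rest on n = 15, 3 mm voxels, 45,000 to 60,000 voxels searched and Gaussian null maps. The mismatch in the wording does not depend on them; its size does.

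**What to change.** Replace the threshold text with one statement: clusters are formed at uncorrected voxel-level P < 0.001, and a cluster is significant only if its SPM12 cluster-level family-wise corrected P is below 0.05, with the critical extent taken from the estimated smoothness and search volume. Delete the 10-voxel sentence, or keep it labelled as an additional reporting minimum that never makes a cluster significant by itself.

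The change costs a sentence and affects neither data collection nor conduct. If the 10-voxel rule would otherwise have been applied by itself, fewer regions may be declared. If the family-wise correction was always meant to decide, deleting the sentence cannot reduce the number of regions declared, and labelling it a reporting minimum changes nothing.
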